#### Security analysis

2.7.3

The safety aspects of this intervention will need to be taken into account, so we will record all adverse events and negative consequences. The safety analysis will include descriptive statistics for all randomized subjects.

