### Study design

2.1

This double-blind, randomized controlled trial will recruit 82 patients with schizophrenia and have a score of ≥12 on the Snaith–Hamilton Pleasure Scale (SHAPS) from the Zigong Affiliated Hospital of Southwest Medical University. Participants will be randomly assigned in a 1:1 ratio to receive either active or sham iTBS, with identical parameters and procedures aside from the stimulation condition. This study is conducted in compliance with the World Medical Association’s Code of Ethics (Declaration of Helsinki). All participants will be fully informed of the study protocol and will provide written informed consent.

Specifically, Individuals expressing interest in the program will first complete a screening questionnaire covering basic demographics and the SHAPS. Those who meet the preliminary inclusion criteria will be invited by their physician to participate. After providing written informed consent, eligible participants will undergo a comprehensive baseline assessment. This assessment includes the collection of clinical data, clinical scale evaluations, WCST, and an fNIRS scan. Following the baseline assessment, participants will be randomly assigned to either the active iTBS group or the sham stimulation group based on the number of randomization in the sealed envelope. The study comprises two phases: a treatment period (15 days) and a follow-up period (4 weeks). All participants in both groups will be evaluated using the SHAPS and the Scale for the Assessment of Negative Symptoms (SANS), and will undergo fNIRS scanning at three time points: before treatment (T0), immediately after treatment (T1), and 4 weeks after treatment completion (T2) (**Figure 1**).

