### Interventions

2.4

The DMPFC treatment target was defined as 25% of the nasion-inion distance in the middle-line of the scalp (32). Stimulation of bilateral hemisphere was accomplished by orienting the coil perpendicular to midline, with current flow directed toward the hemisphere to be stimulated. We use a Classic Magnetic Stimulator YRD CCY-IIB (Yiruide, Wuhan, China).

In the active stimulation group, magnetic stimulation is performed at 90% of the resting motor threshold, with 20 trains of the left and right DMPFC. Preferential stimulation of each hemisphere was accomplished by lateral coil orientation (33). The rTMS target was first randomized to the left or right DMPFC, then switched to the opposite side. (i.e., 40trains, including 20 right side over left side, or 20 left side over right side). The left or right DMPFC were counterbalanced between subjects. Each train consisted of two seconds of stimulation with an eight-second interval. This stimulation consisted of ten 5 HZ clusters with three 50 HZ biphasic pulses in each pulse for a total of 1200 pulses per session. To accelerate the treatment and promote plasticity, a second identical treatment was performed after a 15-minute break (34). The treatment consisted of 30 sessions, administered twice daily over a 15-day period. Sham stimulation was provided to the control group with the coil tilted 90°to the scalp, which produced noise and vibratory sensations similar to real stimuli. And all participants continued their original medication therapy (**Figure 2**).

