### Outcome measurements

2.5

The main outcome measure is the change in scores on the SHAPS. Secondary outcome indicators: 1) The change in the SANS; 2) The change in the Side Effects Scale (SEPS); 3) The change in the Temporal Experience of Pleasure Scale (TEPS); 4) The oxygenated hemoglobin (oxy-Hb) and the deoxyhemoglobin (deoxy-Hb) in the probe and channel at the region of interest-prefrontal cortex, under the near-infrared functional brain imaging task; 5) Results of the Wisconsin Card Test: number of correct, number of incorrect, number of persistent errors, number of nonsustained errors, total number of classifications, and number of items needed to complete the first classification; 6) the Adverse Events (AEs) (**Table 2**).

**Table 2 T2:** Outline of study assessments and timelines.

Assessment tool	Baseline	Post-interventions (Day16)	Follow-up (Day44)
Demographic information	✓		
SHAPS	✓	✓	✓
TEPS	✓	✓	✓
SANS	✓	✓	✓
fNIR	✓	✓	✓
WCST	✓	✓	✓
AEs		✓	✓

SHAPS, the Snaith-Hamilton Pleasure Scale; TEPS, the Scale for the Assessment of Negative Symptoms; TEPS, the change in the Temporal Experience of Pleasure Scale; fNIR, functional near-infrared spectroscopy; WCST, the Wisconsin Card Test; AEs, Adverse Events.

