#### Sample size

2.7.1

This study focuses on the differences in outcomes due to the two populations at the three time points, and the statistical methodology lends itself to the use of repeated measures ANOVA. The dependent variable was set as the measurement outcome. The independent variables were between-groups for the rTMS group and sham rTMS group, and within-groups for the three time points of pre-treatment (T0), post-treatment (T1), and 4 weeks post-treatment (T2). The effect size used to calculate the effect size was 0.25, the significance level alpha was 0.05, the statistical test efficacy was 0.8, and the non-spherical corrected moderate deviation from the spherical hypothesis value was 0.75. We will need a sample size of 66 participants. If the maximum allowable dropout rate is 20%, the total sample size needed for this study would be 82 participants. The sample size calculation was carried out using G*Power version 3.1.9.7_143.

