#### Statistical considerations

2.7.2

Differences in demographic characteristics and clinical variables between the two groups will be compared using t-test for continuous variables and χ^2^ test for categorical variables. The primary and secondary outcomes will be analyzed using linear mixed-effects models, applied on an intention-to-treat basis. In addition, Pearson or Spearman correlations will be used to analyze the correlation of anhedonia with prefrontal activity and cognitive performance. All statistical analyses were performed using SPSS (Version 24.0; IBM Corp., Armonk, NY, USA).

To assess the integrity of blinding, participants were asked at the conclusion of the treatment period to guess their group assignment (active or sham). The distribution of guesses between the two groups was compared using a χ² test. A correct guess rate no better than chance (50%) in both groups would be considered evidence of successful blinding.

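### The safety set is everyone randomized rather than everyone stimulated, so any participant who never starts slightly dilutes the rate of stimulation-related adverse events (minor)

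*Protocol article*

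**What the plan says.** Section 2.7.3 (Security analysis) says that all adverse events will be recorded and then names the population: "The safety analysis will include descriptive statistics for all randomized subjects". It sets no exposure condition, such as at least one session received, and no other section does so.

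The order of events is in section 2.1 (Study design): "Following the baseline assessment, participants will be randomly assigned to either the active iTBS group or the sham stimulation group". Stimulation comes after that step, so the article allows for a participant who is randomized but never stimulated.

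Three other statements bear on size and importance:

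- Section 2.1, allocation: "Participants will be randomly assigned in a 1:1 ratio to receive either active or sham iTBS".
- Section 2.7.1 (Sample size): "If the maximum allowable dropout rate is 20%, the total sample size needed for this study would be 82 participants".
- The Introduction puts safety beside efficacy in the first aim, and section 2.5 lists adverse events among the secondary outcomes.

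**The concern.** Intention-to-treat protects the efficacy comparison because it keeps the groups as randomized. A descriptive safety table asks something different: how often harm occurred among people exposed to the stimulation. Someone who never had a session adds nothing to the numerator for stimulation-related harm but adds one to the denominator. For that class of event the reported rate can only be equal to or lower than the rate among those exposed, which makes the treatment look safer.

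The safety analysis is descriptive, so counts and denominators are its main content. The Discussion also looks ahead to describing the treatment as safe if results are favourable. The article states this population outright. An analysis plan that followed it would carry the same rule, so this is not a detail merely left to a document that is not shown.

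**Working it through.** **Inputs from the article.** Total 82 and a 20% dropout allowance (section 2.7.1); 1:1 allocation (section 2.1); safety set of all randomized participants (section 2.7.3).

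**Inputs not in the article, assumed here.** The number never stimulated per arm, u, taken as 1, 2, 4 or 8; the number of participants with a stimulation-related event, taken as 5 in one arm for illustration; and the true event rate among those exposed, taken as 10%, 30% or 50%.

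**Step 1: the plan's own figure.** The article gives no safety figure to reproduce. The only planned number used here is the total: 66/(1 - 0.20) = 82.5, against the stated 82. The small gap has no bearing on this point. Per arm, 82/2 = 41.

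**Step 2: the dilution factor.** Let e participants in an arm have a stimulation-related event. All of them were stimulated.

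- Reported rate: e/41
- Rate among those exposed: e/(41 - u)
- Reported divided by exposed: (41 - u)/41
- Relative understatement: u/41

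**Step 3: numbers put in.**

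| u per arm | (41-u)/41 | Relative understatement | Reported if exposed rate is 10% | 30% | 50% |
|---|---|---|---|---|---|
| 1 | 40/41 = 0.976 | 2.4% | 9.8% | 29.3% | 48.8% |
| 2 | 39/41 = 0.951 | 4.9% | 9.5% | 28.5% | 47.6% |
| 4 | 37/41 = 0.902 | 9.8% | 9.0% | 27.1% | 45.1% |
| 8 | 33/41 = 0.805 | 19.5% | 8.0% | 24.1% | 40.2% |

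With five events in the arm, the plan reports 5/41 = 12.2%. Among those exposed it would be 5/39 = 12.8% for u = 2, a difference of 0.6 percentage points, and 5/33 = 15.2% for u = 8.

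**Step 4: how plausible each row is.** The last row comes from 20% of 41 = 8.2, rounded to 8, with every one of those participants leaving before the first session. The 20% is a maximum allowance for dropout in a design that runs to a follow-up visit at Day 44 (Table 2). It says nothing about withdrawal before treatment. The first two rows are the more ordinary cases.

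**Step 5: the comparison between arms.** If u is the same in both arms, both rates shrink by the same factor: their ratio is unchanged and their difference shrinks by that factor. If the never-stimulated participants fall mainly in the sham arm, the sham rate is lowered more and the gap widens. The direction of the effect on the comparison is therefore not fixed.

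**The case against.** The strongest reply is that the effect is small and conditional. In a single-site trial with a 15-day treatment period few participants may fail to start, and with two non-starters the change is 0.6 points in a descriptive table. A reader told how many started in each arm could recompute the rate. This stands and is why the point is minor. It does not remove the mismatch between the stated set and the question asked.

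Three stronger readings are tempting, and the article does not support them.

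- **Events after mis-delivered treatment will be counted in the wrong arm.** A reader might infer this by combining the listing of adverse events as a secondary outcome (section 2.5) with section 2.7.2: "The primary and secondary outcomes will be analyzed using linear mixed-effects models, applied on an intention-to-treat basis". But that sentence ties intention-to-treat to outcomes analysed by mixed models, whereas section 2.7.3 gives safety its own descriptive analysis and does not say how events are grouped. Sham differs from active by coil position ("Sham stimulation was provided to the control group with the coil tilted 90°to the scalp"), so an error in delivery is conceivable. The article gives no sign of one, and section 2.3 describes sequentially numbered, opaque, sealed envelopes.
- **The stated set can only understate adverse-event rates and always pulls the arms together.** Section 2.7.3 records all adverse events, so an untreated participant may contribute a background event. The downward direction holds for stimulation-related events only, and step 5 shows that the effect between arms can go either way.
- **The reported rate will be about 20% too low.** That figure needs the entire dropout allowance to be spent before the first session.

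**Conclusion.** The point holds as a minor one. Section 2.7.3 defines the safety population by randomization, section 2.1 places randomization before exposure, and nothing else in the article restricts the set to those exposed. The rate of stimulation-related adverse events is diluted by (41-u)/41 in each arm.

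The size rests on an assumed u, since the article gives none: about 2% relative for one never-stimulated participant per arm, about 5% for two, and about 20% only as an unlikely upper bound. If everyone starts treatment, the dilution is zero. Efficacy results and the sample size are not affected. Grouping by stimulation received is advised only as a precaution, not because the article contains an error of arm assignment.

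**What to change.** Replace the population sentence in section 2.7.3 with wording such as:

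> Safety will be summarized descriptively by arm in all participants who received at least one stimulation session (active or sham), grouped by stimulation received; any participant who received at least one active session is counted as active. Adverse events in randomized but untreated participants will be listed separately.

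Keep intention-to-treat for efficacy. The rule for mixed sessions is needed because treatment runs over 30 sessions, and a single wrong delivery would otherwise leave the participant's group undefined. The change should be made before allocation is revealed.

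The cost is small. Safety denominators may differ from those in the efficacy tables, and rates may look slightly less favourable. The rule also needs a record of which sessions each participant received and of which type. The article does not mention such a record, so the sponsor should confirm that one is kept.

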## Discussion

3

The design of this protocol is based on the following key evidence. Recent studies have shown that rTMS targeting the DMPFC can alleviate anhedonia in depression by improving connectivity within the reward circuitry (15, 35). Anhedonia is a symptom of apathy in schizophrenia, but it is also a core symptom of depression. Some perspectives suggest that the overlap between anhedonia and apathy in schizophrenia can be explained by specific deficits in anticipatory pleasure, while consummatory pleasure experience remains relatively intact (36, 37). The mechanisms underlying anhedonia differ between schizophrenia and depression. As reviewed by Bégue et al., anhedonia in schizophrenia is associated with abnormalities in the prefrontal-striatal network, particularly involving the ventral striatum (VS), ventromedial prefrontal cortex (VMPFC), dorsolateral prefrontal cortex (DLPFC), and anterior cingulate cortex (ACC). Although DMPFC-iTBS has been explored in depression, its application in schizophrenia remains underexplored, representing an innovative strategy for targeting the complex network underlying anhedonia in this disorder (38). Furthermore, previous clinical studies have demonstrated the efficacy of DMPFC-targeted rTMS in schizophrenia with negative symptoms (39). We anticipate that the rTMS intervention in this study will lead to significant improvements in anhedonia among schizophrenia.

Anhedonia is associated with multiple reward processing components, including reward evaluation, anticipation, decision-making, and motivation (40). It is thought to potentially arise from dysfunction in the mesolimbic dopamine pathway and its terminal regions (e.g., striatum, amygdala, and prefrontal cortex) (41). It is noteworthy that these brain regions may also be involved in motivational processing (42), suggesting a possible shared pathological basis between anhedonia and amotivation in schizophrenia. The DMPFC, as a key node within the mesolimbic dopaminergic system (14), may be a promising target for rTMS to ameliorate anhedonia in schizophrenia.

To elucidate the potential neurobiological mechanisms of action, our trial collected cognition-related data, such as prefrontal cortex oxyhemoglobin levels measured via fNIRS. If analyses reveal correlations between improvements in anhedonia and these cognitive metrics, it could offer clues for further explaining the intervention mechanisms of rTMS.

Several limitations of this study should be acknowledged. Firstly, although every effort was made to maintain participant blinding, it is possible that some individuals may have inferred their intervention assignment during the trial based on their prior rTMS experience. Secondly, the study included only a 4-week follow-up period, resulting in a relatively short overall duration and limiting the evaluation of long-term efficacy. Finally, the use of fNIRS to assess brain function in this study is constrained by its limited resolution and penetration depth, which hampers precise localization of neural activity. Future research could incorporate multimodal imaging techniques, such as magnetic resonance imaging, to improve anatomical accuracy and provide deeper mechanistic insights.

In summary, if our study demonstrates that high-frequency iTBS targeting the DMPFC is a safe and effective approach for alleviating anhedonia in schizophrenia, it could offer a novel avenue for treating this symptom in affected patients.

### Test status

3.1

The study is currently ongoing. Recruitment started in January 2025 and will end in December 2025.
